**Fig. 1 Fig1:**
[figure not shown]
The detailed timeline of the study

### Procedures

#### Six-minute walking distance (6-MWD) and Borg scale

Blinded to the patients’ allocation groups, investigators will perform a 6-MWD test, according to the ATS guidelines [52]. Before and after the 6-MWD test, heart rate, blood pressure, and oxygen saturation will be measured. If the patient receives supplemental oxygen, the amount of oxygen has to be the same for each test. After the test, 6-MWD and subjective perception of dyspnea, measured by the Borg scale of 10 points, will be determined.

#### Cardiopulmonary exercise testing (CPET)

Cardiopulmonary exercise testing will be performed to assess peak oxygen uptake (peak VO_2_), peak VO_2_/kg, peak workload, heart rate, blood pressure, oxygen saturation, ventilation, ventilatory equivalent for carbon dioxide (VE/VCO_2_), VO_2_, and VCO_2_ at the anaerobic threshold. Investigators will be blinded to the patients’ allocation group.

#### Echocardiography

Investigators, blinded to the patients’ allocation groups, will perform echocardiography. Two-dimensional, Doppler echocardiography, and three-dimensional (3D) measurements will be conducted. Echocardiography measurements will include sizes of chambers, LV pump function (LV ejection fraction, determined by Simpson biplane method and 3D LV EF), LV diastolic function (*E*/*e*′ mean), RV pump function (RV fractional area change (FAC) and 3D RV EF), estimated systolic pulmonary arterial pressure (sPAP), tricuspid annular plane systolic excursion (TAPSE), tricuspid annular peak systolic velocity (TAPSV), global longitudinal RV and LV strain, and size and collapsibility of the inferior vena cava (IVC).sPAP will be estimated by the maximal velocity of tricuspid regurgitation using the Bernoulli formula. Right atrial pressure will be evaluated under consideration of IVC: 3 mmHg if the vena cava < 21 mm (width) and collapses during inspiration > 50%, 8 mmHg if the vena cava is > 21 mm and collapses during inspiration > 50%, and 15 mmHg if the vena cava is > 21 mm and collapses < 50%.

#### Invasive hemodynamic assessment (optional)

Hemodynamic parameters will be determined by right heart catheterization according to the current guidelines. Invasively measured parameters will include right atrial pressure, mean pulmonary arterial pressure (mPAP), and pulmonary artery wedge pressure (PAWP). Cardiac output (CO) will be estimated by the thermodilution method. Pulmonary vascular resistance (PVR) and cardiac index (CI) will be calculated. The values will be based on two to three measurements at one time point. Hemodynamics will be measured at rest and optionally during exercise with a supine bicycle ergometer. Investigators will be blinded to the patients’ allocation group.

#### Cardiac MRI (optional)

Investigators who will be blinded to the clinical data and group assignment will evaluate cardiac MRI. MRI measurements will include LV and RV mass, area, volumes and function (regional and global), diastolic function assessment (mitral-pulmonary flows), atrial size and function (left atrial strain and strain rate), T1 mapping/extracellular volume, and the pulmonary artery to aorta ratio.

#### Laboratory parameters

The N-terminal prohormone of brain natriuretic peptide (NTproBNP) will be assessed at baseline and after the 15-week follow-up period. Routine laboratory parameters determined according to the standards of the clinic (hemoglobin, glucose, creatinine, potassium, iron) will be collected as safety parameters.

#### Patient-reported outcomes

Quality of life will be assessed with the 36-Item Short Form Health Survey (SF-36) [53]. The questionnaire includes two main scores with physical component and emotional component scales and eight subscales. A higher score indicates a better QoL. Anxiety and depression will be assessed using the Hospital Anxiety and Depression Scale (HADS) [54]. The HADS comprises seven questions for anxiety and seven questions for depression. Scores of less than 7 indicate non-anxiety or non-depression. The higher the score, the more pronounced anxiety or depression is. Both questionnaires will be in the respective language of the country.

#### Risks assessment

Adverse reactions/adverse events and serious adverse reactions/serious adverse events will be documented throughout the trial.

### Statistical considerations and analyses

#### Sample size calculation

To estimate the effect of exercise training on 6-MWD, 90 patients are expected to be enrolled, who either receive exercise training or continue their daily lifestyle for 15 weeks. The sample size was calculated by the G*Power 3.1 program according to the results of previous studies on 6-MWD. Based on previous data and the inclusion criteria, we expect a clinically significant mean increase of 35 m with a standard deviation of the difference of 50 m. If the true treatment effect is a difference of at least 35 m with an equal standard deviation of the difference of 50 m, the two-sided Student’s *t*-test at an alpha level of 0.05 has a power of 85%, if 38 patients for each group are included. To account for a possible 15% dropout rate, we will include 45 patients in each group—90 patients in total.

#### Statistical analysis

The data from all centers will be pooled. If sample sizes allow, center effects on the primary and secondary outcomes will be analyzed.

Descriptive statistics will be displayed by treatment and control groups corrected for the active treatment group, including the usual location and scale statistics (mean, median, standard deviation, standard error, first and third quartiles, minimum, and maximum) and 95% confidence limits of the mean and median. Frequency tables for qualitative data will be provided. As an unbalanced distribution of baseline characteristics may not be completely excluded, baseline clinical parameters including patient risks and prognostic implications will be analyzed and compared between the groups.

The primary efficacy analysis will be based on an analysis of variance with the baseline values as a covariate (ANCOVA). This analysis provides a power advantage over the standard two-sided Student’s *t*-test leading to a statistical power of 85% or more. If the preconditions for ANCOVA are not met, a *t*-test with robust variance estimation (Welch test) will be used. Secondary endpoints will be analyzed by comparison of the mean changes between baseline and 15 weeks in the two groups (training vs control group) adjusted for the baseline value (ANCOVA or Wilcoxon rank sum test for non-parametric data). Categorical data will be analyzed by the McNemar test or chi-square test as appropriate. Exploratory data analysis of follow-up will be conducted by descriptive statistics and comparing baseline values and follow-up examinations. In case of ≤ 20% of missing values of a variable, a multiple imputation strategy will be used and analyzed as sensitivity analysis for data interpretation. The primary analysis set is the intention-to-treat analysis population (all patients randomized into the study). As a sensitivity analysis, the per-protocol population will be analyzed (all patients actually taking part in the study). Patients not fulfilling the inclusion criteria will be excluded in a separate sensitivity analysis using the per-protocol set.

Patient characteristics and efficacy parameters (secondary and exploratory endpoints) will be analyzed at baseline and 15 weeks. The values for each respective group will be displayed as mean ± standard deviation or mean ± standard error of the mean. Changes from baseline to 15 weeks will be analyzed by robust Student’s *t*-test (Welch test). Frequency data will be displayed as *n* and %. This data will be analyzed by the chi-square test and McNemar test. By means of correlation and regression analysis, the influence of different factors on the training effect will be investigated. *P*-values < 0.05 will be considered significant.

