### Randomization and blinding

The distribution of patients to the different groups will be performed by block randomization. Group allocation will be provided in sealed envelopes, which will be prepared for each participating center by the study coordinator at Heidelberg University. Blocks for block randomization will be medium size to allow a balanced randomization sequence over time. Sites that only include a very small amount of patients may lead to a minimally unbalanced patient number. Block sizes will be the same for all centers, leading to several randomization/allocation blocks in high recruiting centers. Upon inclusion, the participants will be randomly designated to the intervention (training) or conventional (control) group. Allocation concealment will be ensured, as envelopes will not be unsealed until the patient has been recruited into the trial.

The participation in this rehabilitation program is voluntary. Participants may terminate their participation at any time.

According to the eligibility criteria, the patient should be receiving optimized and ≥ 1 month of stable treatment before inclusion in the study. Thus, we expect that the need for medication changes during the 15-week follow-up period will be minimal. However, the dosage of diuretics is permitted to be changed, and other pharmacological and non-pharmacological treatments will not be prohibited, if the treating physicians decide this to be clinically necessary. Participation in another interventional study is prohibited during the 15-week follow-up period.

Cardiologists, pulmonologists, and PH experts, blinded to the patients’ allocation groups, will perform and interpret examination tests (6-min walking test, cardiopulmonary exercise test, echocardiography, right heart catheterization, cardiac magnetic resonance imaging). Study data analytics will also be blinded to the patients’ allocation groups until the entire analysis has been completed.

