### Interventions

#### Training

The training will be based on the specialized low-intensity rehabilitation program, including exercise and respiratory therapy and mental gait training, which has been previously described [32, 35, 50, 51].

The initial phase of exercise training will be closely monitored, as it will be held in hospital for approximately 3 weeks period and later will be continued for further 12 weeks at home. In-hospital stays will be arranged country-specific, and hospitalization times may range. The rehabilitation program will comprise interval ergometer training (20 min 5 days per week), dumbbell training of single muscle groups (30 min 5 days a week), respiratory therapy (30 min 5 days per week), mental training and guided walks (individually, at least two times a week), and conventional elements, such as massages, relaxation, lectures, and patient education.

Individual training adjustment will be performed according to clinical assessments at baseline and follow-up and the patient’s subjective perception throughout the program. Training intensity will be started at 40–50% of the maximal patient’s workload, reached during the cardiopulmonary exercise test at baseline, and will be increased within the in-hospital period, trying to achieve the maximal baseline workload (maintaining 60–80% of the peak heart rate and avoiding desaturation < 90%). Overexertion must be strictly avoided. In order to ensure safety and adherence, every workout will be supervised by a physiotherapist during an in-hospital phase. Before leaving the hospital, each patient will receive individualized written recommendations on how to continue exercising at home. The patient will be asked to document daily trainings (intensity, duration, pulse rate, blood pressure, adverse events), which will be discussed at the follow-up visits.

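### Allocation is blocked within centre, but the stated primary ANCOVA adjusts only for baseline 6-MWD, so the analysis does not follow the randomisation and is mildly conservative if centre matters

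*Protocol article*

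**What the plan says.** Randomization and blinding describes the design. It gives the method first: "The distribution of patients to the different groups will be performed by block randomization". On how the allocations reach the sites, it says: "Group allocation will be provided in sealed envelopes, which will be prepared for each participating center by the study coordinator". On the blocks themselves, it adds: "Block sizes will be the same for all centers, leading to several randomization/allocation blocks in high recruiting centers". The same section accepts that sites with very few patients may end slightly unbalanced. That remark makes sense only if the blocks run within centres.

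Statistical analysis gives the model: "The primary efficacy analysis will be based on an analysis of variance with the baseline values as a covariate (ANCOVA)". No other covariate is named. The Welch test that replaces the ANCOVA if its assumptions fail has no centre term either, and the ANCOVA for continuous secondary endpoints is adjusted only for the baseline value. Centre appears in one place: "The data from all centers will be pooled. If sample sizes allow, center effects on the primary and secondary outcomes will be analyzed". The section does not say what sample size would suffice, or whether such an analysis would supplement or replace the primary model.

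**The concern.** Blocking within centre forces the arms to be nearly equal in each centre, so differences between centres largely drop out of the true sampling variance of the treatment difference. A model without centre does not know this. It leaves the between-centre variance in the residual and reports a standard error that reflects simple rather than stratified randomisation. The confidence interval is then wider, and the p-value larger, than the design warrants.

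The wording on centre also leaves open whether and how centre is examined until the number and size of the centres are known. Population sampling says the site list will be updated continuously. At stake are a little precision and a clear statement of the primary model. The validity of the test is not at stake.

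**Working it through.** **Inputs from the protocol article (Sample size calculation).** Difference 35 m, SD of the difference 50 m, two-sided alpha 0.05, 38 completers per group, 85% power, 15% dropout, 45 per group enrolled.

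**Assumptions not in the documents.** The share of outcome variance due to centre after baseline adjustment (ICC), the number of centres, and the block size, which is described only as medium.

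**Step 1: the plan's own figure.** SE = 50 × √(2/38) = 11.47 m, and the non-centrality is 35/11.47 = 3.05 on 74 degrees of freedom. The non-central t distribution gives power 0.8535 at 38 per group and 0.8439 at 37, so 38 is the smallest sufficient number. 38/0.85 = 44.7, rounded up to 45 per group and 90 in total. The stated sample size reproduces.

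**Step 2: standard error under ideal within-centre balance.** The model without centre reports about 11.47 m whatever the ICC. The true SE is 11.47 × √(1 − ICC), so the ratio of reported to true SE is 1/√(1 − ICC).

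| Assumed ICC | True SE (m) | Reported SE too large by |
|---|---|---|
| 0 | 11.47 | 0% |
| 2% | 11.36 | 1.0% |
| 5% | 11.18 | 2.6% |
| 10% | 10.88 | 5.4% |
| 20% | 10.26 | 11.8% |

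**Step 3: size and power on a matched comparison.** Both analyses must be judged at the same ICC, because the analysis without centre also benefits from the balanced design. It rejects when the correctly scaled t statistic exceeds t(0.975, 74)/√(1 − ICC), with non-centrality 35/(true SE). The model with centre uses the ordinary critical value with degrees of freedom reduced by the number of centres minus 1. With 4 centres assumed:

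| Assumed ICC | Type I error without centre | Power without centre | Power with centre | Gain (points) |
|---|---|---|---|---|
| 0 | 0.050 | 0.8535 | 0.8531 | 0.0 |
| 5% | 0.0445 | 0.8595 | 0.8703 | 1.1 |
| 10% | 0.0391 | 0.8658 | 0.8873 | 2.2 |

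**Step 4: simulation with imperfect balance.** 76 completers, unequal centres, assumed block size 6, centre fitted as unpooled fixed effects.

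| Centres | ICC | Mean reported SE without / with centre (m) | Power without / with centre |
|---|---|---|---|
| 4 | 5% | 11.42 / 11.23 | 0.854 / 0.856 |
| 4 | 10% | 11.34 / 10.97 | 0.870 / 0.885 |
| 8 | 5% | 11.43 / 11.36 | 0.858 / 0.862 |
| 8 | 10% | 11.42 / 11.07 | 0.863 / 0.872 |
| 11 | 0 | 11.53 / 11.85 | 0.849 / 0.827 |
| 11 | 5% | 11.44 / 11.51 | 0.861 / 0.854 |

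With 8 centres and ICC 10%, the true SE of the analysis without centre was 10.90 m against 11.42 m reported. That is an excess of 11.42/10.90 − 1 = 4.8%, slightly below the 5.4% of step 2. Its type I error was 0.043, against 0.052 with centre. The simulation carries sampling noise: with 2 centres and ICC 0, where reported and true SE should agree, they were 11.47 and 11.70 m. The small contrasts show direction and order of size only.

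**The case against.** Several arguments count against making much of this.

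- **The condition on sample size has a reason.** The plan expects sites with very few patients. With 11 mostly small centres, unpooled fixed effects cost precision when centre explains little (step 4). This stands, and it shapes the fix.
- **The size is unknown.** Neither the ICC nor the number of centres is given, and at ICC 0 nothing is wrong with the standard error. This stands.
- **The reasons to expect a centre effect are modest.** The Training section says "In-hospital stays will be arranged country-specific, and hospitalization times may range". A reader might take this as evidence of a centre main effect. But controls receive no training, so variable stays bear mainly on treatment-by-centre differences, which a main effect does not model. Walk tests are done locally, but to one guideline and by blinded assessors. Stable differences in level between sites largely cancel in a change score adjusted for baseline.
- **A reader might infer that the test is invalid or the trial underpowered.** The error runs the other way: type I error falls below 0.05 and power does not drop below the planned 85%. Comparing 87% to 89% power with centre against the planned 85% would roughly double the apparent gain, because 85% is the power when centre explains nothing.
- **A reader might infer that the primary model can be picked after seeing the result.** The text does not go that far. It names the primary ANCOVA separately, does not say that centre would enter it, and keeps the analysts blinded to allocation until the analysis is complete.
- **An analysis plan not shown may add covariates.** It may, but the article does not leave the model open. It states one, and that one omits the stratum.

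**Conclusion.** The point holds as a matter of efficiency and prespecification. The randomisation is stratified by centre and the stated primary analysis is not. If centre explains 2 to 10% of the variance after baseline adjustment, the reported standard error is about 1 to 5% too large under ideal balance, and less with unequal centres and dropout. The matched power gain from including centre is about 1 to 2 points at an ICC of 5 to 10% with few centres, and nil or negative with many very small ones. These figures rest on an assumed ICC and assumed numbers of centres. The documents support neither an inflated type I error nor a threat to the 85% power, and the sample size needs no change. The change is still worth making, because it aligns the analysis with the design and settles how centre is handled before the data are seen.

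**What to change.** State the primary model as change in 6-MWD at week 15 on treatment, baseline 6-MWD and centre, and use the same form for the continuous secondary endpoints. Enter centre in one of two ways, chosen now:

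- as a random effect; or
- as a fixed effect, with centres too small to fill a block pooled by a rule fixed before unblinding, for example within country. The rule should apply to whichever countries recruit. Table 1 lists Germany and Lithuania, but the site list may grow.

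Keep treatment-by-centre as the exploratory analysis to be done where numbers permit.

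The cost is one or two sentences and a few degrees of freedom, with no extra patients. If centre explains nothing, the loss with 4 well-filled centres is negligible (power 0.8531 against 0.8535). With 11 mostly small centres entered unpooled, the simulated loss was about 2 points (0.849 to 0.827), which is what the pooling rule or random effect is meant to limit.

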### Assessments

#### Efficacy assessment

Efficacy parameters in both groups will be assessed at baseline and after 15 weeks (mean or median changes from baseline to 15 weeks, comparing changes within trained and control groups as well as mean/median changes between these groups). Patients in the training group will additionally perform the 6-MWD at the end of in-hospital rehabilitation.

The primary endpoint is to determine the effect of standardized exercise and respiratory training on exercise capacity, measured by the mean change of 6-MWD (baseline vs 15 weeks vs control group) in the HFpEF-PH population.

Secondary endpoints include mean/median changes from baseline to 15 weeks of echocardiography parameters, cardiopulmonary exercise testing, World Health Organization (WHO) functional class, measurement of safety parameters, health-related quality of life assessment (SF-36 questionnaire), anxiety and depression assessment (HADS scale), optional right heart catheterization at rest and during exercise, and optional cardiac magnetic resonance imaging (MRI). A detailed description of the evaluative parameters of each test is provided in the following paragraph (the “Procedures” section).

A follow-up interview will be performed by phone at the end of the study (last patient, last visit) to assess safety and compliance and observe survival. The long-term compliance and risk profile of exercise training will be explored to identify risk factors and record adverse events.

The detailed timeline of the study is shown in Fig. 1.

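### The primary fallback drops the baseline covariate after an unnamed check, and the plan gives two conflicting tests for the continuous secondary endpoints

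*Protocol article*

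**What the plan says.** All references are to the protocol article.

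- **Primary endpoint.** The Efficacy assessment section defines exercise capacity as "measured by the mean change of 6-MWD (baseline vs 15 weeks vs control group"), that is, the change in 6-minute walk distance compared between arms.
- **Primary test.** The third paragraph of Statistical analysis uses ANCOVA with baseline as covariate. It claims a power advantage over the Student t-test, "leading to a statistical power of 85% or more". It continues: "If the preconditions for ANCOVA are not met", a Welch test is used instead. No precondition, check or threshold is given.
- **Secondary endpoints, first rule.** The same paragraph compares changes between arms "adjusted for the baseline value (ANCOVA or Wilcoxon rank sum test for non-parametric data").
- **Secondary endpoints, second rule.** The fourth paragraph, which covers secondary and exploratory efficacy parameters, states without condition: "Changes from baseline to 15 weeks will be analyzed by robust" Student's t-test, identified as the Welch test.
- **Planned power.** The Sample size calculation section assumes "a difference of at least 35 m with an equal standard deviation of the difference of 50 m". It says that a two-sided Student t-test "at an alpha level of 0.05 has a power of 85%, if 38 patients for each group are included".

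**The concern.** There are two separate faults.

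**The primary fallback.** The primary test depends on an unspecified check of the trial data, and the alternative gives up the covariate that justified ANCOVA. None of the usual departures calls for that. In a 1:1 randomized trial, ANCOVA still estimates the mean treatment difference when variances differ, residuals are non-normal or slopes differ between arms. Heteroscedasticity-robust standard errors deal with the inference. The section itself says that baseline imbalance cannot be fully excluded, so removing the covariate sits badly with its own reasoning.

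**The secondary endpoints.** Two adjacent paragraphs assign different tests to the same continuous endpoints. The first is internally strained as well: a rank sum test, as named, carries no baseline covariate, yet it is listed as a way to adjust for baseline. With both rules in the text, an analyst can call either p-value planned.

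At stake are efficiency in the primary analysis and analyst discretion in the secondary ones.

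**Working it through.** **Inputs from the Sample size calculation section:** difference 35 m; SD of the change 50 m, equal in both arms; two-sided alpha 0.05; 38 evaluable per arm; 15% dropout. **Assumed, because the article does not give it:** the correlation ρ between baseline and week-15 distance, taken from 0.5 to 0.95, with equal SD at both visits.

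**1. Reproduce the plan's figure.** Unadjusted t-test on the change:

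- Noncentrality = 35 / (50 × √(2/38)) = 35 / 11.47 = 3.05, with 74 degrees of freedom.
- Power from the noncentral t distribution = 85.3% (37 per arm gives 84.4%).
- 38 / 0.85 = 44.7, rounded up to 45 per arm, 90 in total.

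The stated design reproduces. The 85% belongs to the unadjusted test. With equal arms and equal SDs, Welch on the change has practically the same power.

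**2. Power of ANCOVA.** If the SD of the change is 50, the SD at each visit is 50/√(2(1−ρ)). The ANCOVA residual SD is then 50 × √((1+ρ)/2), with one degree of freedom fewer.

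| ρ | Residual SD (m) | ANCOVA power | Welch on change | Advantage (points) |
|---|---|---|---|---|
| 0.5 | 43.3 | 93.5% | 85.3% | 8.2 |
| 0.7 | 46.1 | 90.4% | 85.3% | 5.1 |
| 0.9 | 48.7 | 87.1% | 85.3% | 1.8 |
| 0.95 | 49.4 | 86.2% | 85.3% | 0.9 |

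**3. The switching rule, simulated.** Since the article names no checks, three were assumed, each at 5%: Shapiro, Levene and a slope interaction. There were 38 per arm and 4,000 runs per setting (Monte Carlo error of the type I rates about 0.35 points). With normal data and equal SDs, about 14% of trials switched.

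| ρ | Power: ANCOVA always | Power: switching rule | Type I error: switching rule | Type I error: smaller of the two p-values |
|---|---|---|---|---|
| 0.6 | 92.0% | 91.3% | 5.7% | 8.1% |
| 0.8 | 87.7% | 87.0% | 4.4% | 5.8% |
| 0.9 | 86.1% | 85.8% | 5.0% | 6.1% |

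At ρ = 0.6 ANCOVA alone gave 5.5% and Welch alone 5.6% in the same runs, so the 5.7% is no sign of inflation by the switch. Averaged over trials, the rule costs less than 1 point of power here, because it seldom switches.

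**4. When the data depart from the assumptions.**

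- Skewed residuals, ρ = 0.8: every trial switched. Power was 83.9% under the rule against 87.5% with ANCOVA always.
- Unequal slopes, ρ = 0.7, slope difference −0.3, 5% slope test: 41% switched. Power was 84.0% under the rule against 88.1% with ANCOVA always and 87.5% with HC3 robust errors.
- Slope difference +0.3: again 41% switched, but power was 87.7% under the rule against 87.8%.
- Training-arm residual SD 1.5 times larger, ρ = 0.8: 67.8% under the rule, 69.1% with ANCOVA always. The noise lowers both; the switch adds little.

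In the unequal-slope simulations, ANCOVA with HC3 errors held type I error at 3.9 to 5.0%.

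**The case against.** The strongest reply is that nothing promised is lost. The 85% was calculated for the unadjusted test, and Welch on the change keeps it. That stands. A reader might infer from the fallback that the trial becomes underpowered, but the Sample size calculation section does not support this. A figure near 77% can be produced, but only by applying Welch in every trial under a slope difference of −0.3, which raises the training-arm SD of change to about 60 m, against the planned equal 50 m. The rule as written gives about 84% there, and the opposite slope direction costs almost nothing. The article indicates no direction.

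A reader might also infer that the switch inflates type I error or leaves baseline imbalance uncorrected. Neither follows. The simulations show no clear inflation. Because the endpoint is a change, Welch already subtracts baseline with coefficient 1; this is less efficient than ANCOVA but not unadjusted in that sense, and randomization keeps it unbiased.

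Three defences succeed only in part:

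- **The analysis plan may name the checks and thresholds.** It may, and their absence from an article is not the complaint. The article does fix the replacement test, and that choice is the weak one.
- **Analysts stay blinded until the analysis is complete** (Randomization and blinding section). This helps, but two-sided p-values from coded groups are the same, so blinding does not settle which test counts.
- **The Welch sentence might mean within-group change.** The Efficacy assessment section does mention such comparisons. But Welch compares two independent samples, so on that reading the named test would be wrong. The paragraphs need reconciling either way.

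**Conclusion.** The point holds as a moderate one that should be fixed. The primary fallback gives up baseline adjustment for reasons that do not require it, and the third and fourth paragraphs of Statistical analysis conflict on the continuous secondary endpoints.

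The loss in a trial that switches is the ANCOVA advantage, about 8, 5 and 1 points at assumed correlations of 0.5, 0.7 and 0.95. The stated 85% survives under the planned equal SD of 50 m. For a secondary endpoint, the conflict would allow a type I error of about 6 to 8% if the smaller of the ANCOVA and Welch p-values were reported. That is the effect of unrestricted choice; nothing in the article says such a choice is intended. The two faults also differ in kind: in the first the data select the test, in the second the text leaves it to the analyst.

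These sizes rest on the assumed correlation, on equal SDs at both visits and, for the switching results, on the three assumed checks.

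**What to change.** 1. Make ANCOVA with baseline as covariate and heteroscedasticity-robust standard errors (for example HC3) the single primary analysis, and remove the precondition switch.
2. Apply the same rule to every continuous secondary endpoint.
3. Delete the Welch sentence in the fourth paragraph of Statistical analysis, or reconcile it with the third. If within-group change was meant, say so and name a paired method.
4. Keep Welch and Wilcoxon as labelled sensitivity analyses that do not replace the main result.

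The cost is a few sentences, with no extra patients or data, provided the change is made before unblinding. Robust errors cost about 1 point of power (87.5% against 88.1% in the unequal-slope simulation above).
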